AFAST score 1 (GEA score): increase of 2 points in the score at the previous visit, in the case of success, orAFAST score 2 (mandibular score): increase of 1 point in the score at the previous visit, in the case of success
Number of patients with reappearance of 10% or more of inflammatory lesions at M6

For these nine outcomes, percentages will be calculated at each time point:
Quality of life (QoL): reporting of the scores of two QoL questionnaires: the Euroqol-5 dimensions (EQ-5D) and the Cardiff Acne Disability Index (CADI) at M2, M4, M6, M9 and M12. This outcome will be measured by the percentage of patients whose quality of life has improved relative to baseline.Microflora: bacterial and parasitic sampling at D0 and M4. The presence *of P. acnes, M. Furfur* and *S. epidermidis/ aureus* will be sought and a change in these populations from baseline will be measured at M4. A percentage of decrease will be calculated.Medico-economy: incremental cost-effectiveness ratio (cost per quality-adjusted life year (QALY)) of the comparison between spironolactone and cycline at 6 months. Criteria for the calculation of the cost-effectiveness ratio are detailed in “Methods for additional analyses”.

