With regard to the study questionnaires, we will use the EQ-5D and the CADI. The EQ-5D questionnaire, validated in France [46], will be given to the patient at each visit to measure their quality of life. The EQ-5D consists of a questionnaire and a visual analogue scale. The questionnaire focuses on 5 dimensions: mobility, personal autonomy, current activities, pain/discomfort and anxiety/depression. For each of these dimensions, three answers are possible (EQ-5D-3 L), thus allowing for 243 health states. The CADI is a disease-specific questionnaire measuring disability induced by acne [47]. It is a well-known acne disability measure and has been used in some studies to assess the burden of living with acne on a patient’s experience of disability [48, 49]. The questionnaire was developed as a multidimensional measure related to the impact of acne [50]. It is a 5-item scale: questions 1 and 2 address the psychological and social consequences of acne in general; question 3 is targeted at those with acne of the chest or back; question 4 enquires about the patient’s psychological state; and question 5 asks for the patient’s (subjective) assessment of their current acne severity. The response to each question is scored from 0 to 3. CADI is validated by our team in French [51].

Bacterial and parasitic samples will be collected from the nodulocystic and pustular skin of the participants at D0 and M4, using an Eswab to be delivered in an AMIES transport environment (1 ml). The analysis will be centralized at Nantes University hospital and performed by [name].

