### Statistical methods

#### Statistical methods for primary and secondary outcomes {20a}

The primary efficacy variable is the percentage of success defined in “Background and rationale” (paragraph 2.1.2). The comparison between the two arms will be done using a Cochran–Mantel–Haenszel test checking for class of contraception (four strata). Modified intention to treat (ITTm) andlysis will be applied. That implies that to maintain the initial statistical power of the ITTm analysis, all randomized patients will be included in the final analysis, minus those who did not fulfil the inclusion criteria after randomization and those who never began their treatment.

All secondary objectives are expressed as a percentage or a status at a fixed time of follow up. General linear mixed models will be planned to take into account the repeated measurements collected on the same participant during their follow up. The Cox model with time-dependent covariates can also be used for secondary objectives for which a status is considered. Significance will be set at 5% in a bilateral situation.

For the cost-effectiveness analysis, 95% confidence intervals for differential (between arms) costs and QALYs and for the incremental cost-effectiveness ratio (ICER) will be estimated using the non-parametric bootstrap estimation procedure.

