### Methods for additional analyses (e.g. subgroup analyses) {20b}

An economic evaluation taking the form of a cost-effectiveness analysis (CEA) will be conducted to compare the efficiency of spironolactone and cycline treatment. The analysis will be conducted from the societal perspective, which means that costs to hospitals, the National Health Insurance System and patients will be considered, over a 6-month time horizon, to be consistent with the primary endpoint. The main judgement criterion will be the incremental cost-effectiveness ratio defined as a cost per QALY gained. To estimate QALYs, patients will be asked to fill in the EuroQol EQ-5D health-related quality of life questionnaire.

For the estimation of costs, resources consumed will be recorded prospectively in the patient’s diary for a period of 6 months following the start of the treatment. The main resources to be collected are in the patient diary are: * Medication * Ambulatory physician visits * Dermocosmetic care.

Unit costs will be estimated using conventional tariffs from the French National Health Insurance System to value ambulatory care consumption. Costs in each arm will be estimated by multiplying the amount of each type of resource consumed by their corresponding unit monetary value. In CEA, the outcomes of an intervention are evaluated in terms of the QALY, which is a numerical composite measure that encompasses information about the length of life and the health-related quality of life. They are computed by weighting each year by a corresponding quality of life factor, usually ranging from 0 (death) to 1 (perfect health). Quality of life weights will be obtained by asking patients to answer the EuroQol EQ-5D quality of life questionnaire at baseline and at 2, 4, and 6 months from baseline. The difference in QALYs between the two arms of the study will be calculated using analysis of area under the curve, with linear interpolation of utility scores between measurement time points.

The EQ-5D will also be applied at 9 and 12 months to evaluate quality of life up to M12, as a secondary objective, independently from the cost-effective analysis. The ICER (see below) comparing the spironolactone and cycline arms will be analysed using a non-parametric bootstrap approach to produce estimated confidence intervals at 95% over the mean ICER:

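### Quality of life is compared as percent improved with no threshold although scores are collected, and the model and scale named for other secondary outcomes do not fit them

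*Protocol article*

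**What the plan says.** Three statements in the protocol article matter here.

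- **Quality of life.** Outcomes {12} lists "reporting of the scores of two QoL questionnaires", the EQ-5D and the CADI, at M2, M4, M6, M9 and M12. It then fixes the measure: "This outcome will be measured by the percentage of patients whose quality of life has improved relative to baseline". Section {18a} describes the instruments. The CADI has five items, and "The response to each question is scored from 0 to 3". The EQ-5D-3L has five dimensions with three levels each, plus a visual analogue scale.
- **Other efficacy outcomes.** After the list of secondary efficacy outcomes, Outcomes {12} says: "For these nine outcomes, percentages will be calculated at each time point".
- **Model.** Section {20a} says "All secondary objectives are expressed as a percentage or a status at a fixed time of follow up", and then "General linear mixed models will be planned to take into account the repeated measurements collected on the same participant during their follow up". It adds that a Cox model may be used where a status is considered.

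One analysis keeps the EQ-5D numeric. Section {20b} computes QALYs to 6 months as an area under the curve, "with linear interpolation of utility scores between measurement time points".

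**The concern.** A score that has been collected on every woman at every visit is reduced to improved or not before the arms are compared. As worded, a one-point fall on a CADI total of 0 to 15 counts the same as a ten-point fall. With two questionnaires and a visual analogue scale, it is also open which of them determines that a woman has improved. The Discussion predicts a large quality-of-life benefit, so the measure meant to test that prediction should not waste data.

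The other two statements raise a related question of fit. A general linear mixed model, in the ordinary sense of the term, assumes normal errors. The section pairs it with outcomes it has just described as percentages or statuses. And a percentage at each time point makes sense for a number of patients, but not without further definition for a number of lesions.

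**Working it through.** **1. The plan's own sample size.** Sample size {14} gives 70% against 50% success, 5% type I error, 80% power and 91 per group; {20a} makes the test two-sided. The unpooled two-proportion formula gives

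n = (0.70×0.30 + 0.50×0.50) × (1.960 + 0.842)² / 0.20² = 90.3, rounded up to 91.

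The stated figure is reproduced. It concerns the primary endpoint only; no power is claimed for quality of life. It is used below only as the number of women per arm.

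**2. Cost of cutting the quality-of-life score.** The protocol gives neither the distribution of the change score nor the share of women who improve. Two assumptions are therefore needed: a roughly normal change score with equal SD in both arms, and a share p improving (averaged over arms) of 50% to 80%, with 90% added as an extreme.

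The efficiency of the binary comparison relative to the comparison of means is φ(z_p)² / [p(1−p)], where φ is the standard normal density and z_p the normal quantile of p. For p = 0.5 this is 0.3989² / 0.25 = 0.637.

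With 91 per group, a comparison of means has 80% power for a standardised difference of (1.960 + 0.842) × √(2/91) = 0.415. The same effect, cut to improved or not, gives:

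| Share improved | Information kept | Power at 91 per group | n per group for 80% power |
|---|---|---|---|
| 50% | 0.64 | 60% | 144 |
| 70% | 0.58 | 56% | 160 |
| 80% | 0.49 | 49% | 189 |
| 90% | 0.34 | 36% | 274 |

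With 100 per group the detectable standardised difference is 0.396, and the powers agree to within 0.2 percentage points.

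**3. A normal-errors model on yes/no data.** The between-arm contrast at a single visit was simulated 40,000 times per setting with an ordinary least-squares test. With 91 or 100 per arm and true rates from 5% to 70%, type I error was between 4.2% and 5.9%. Power for 70% against 50% was 79.5% at 91 per arm and 83.3% at 100, against 79.1% and 82.8% for the two-proportion test. The repeated-measures model itself was not simulated.

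**4. The nine efficacy outcomes.** Five are numbers of patients: AFAST score 1 at 0 or 1, AFAST score 2 at 0 or 1, both scores at 0 or 1, relapse, and reappearance of inflammatory lesions. Percentages are natural for these. Four are not: inflammatory, retentional and total face lesions are counts, and trunk lesions are an ECLA F2 score. For these four, the sentence on percentages names no numerator or denominator.

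**The case against.** The strongest reply is that most of this is wording or detail for an analysis plan that is not shown. A responder percentage is a recognised and readable summary. The quality-of-life scores are also to be reported, and the QALY analysis keeps the EQ-5D numeric, so the data are not thrown away. The word general may be a slip for generalised. Link functions, distributions and covariates are normally settled in the analysis plan.

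Much of that is fair, and it rules out several stronger readings that a reader might infer:

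- **That every secondary outcome is a percentage under a normal model.** Section {20a} says percentage or status and allows a Cox model; safety reporting and the cost-effectiveness analysis are separate.
- **That lesion counts are dichotomised and lose precision.** The document never says so. A percentage there could mean percent change, as it does for the microflora item, so the information-loss figures do not apply to lesions.
- **That a normal model gives wrong standard errors.** At a single visit, the simulated error rate stayed near 5%.
- **That a woman with no EQ-5D problems at baseline is scored a failure.** No denominator is given, and analysing the score would not remove the ceiling either.
- **That the trial loses a fixed number of its 200 women.** Any such figure rests on assumed rates and concerns quality of life only.

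What survives is not an omission. The protocol states that quality of life is measured by percent improved, and reporting the scores alongside does not change the measure on which the outcome is defined. It names a model family that, read literally, does not match the outcomes it is attached to. And it promises percentages for outcomes that have none defined.

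**Conclusion.** The concern holds in a limited form. The quality-of-life outcome is fixed as an improved-or-not percentage, with no size of change and no statement of which instrument decides, although scores are available. Under a roughly normal change score and 50% to 80% improving, the comparison keeps about 64% to 49% of the information. Both conditions are assumptions. The EQ-5D-3L and the CADI are coarse scales, so the figures indicate the order of the loss rather than its exact size.

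The model wording is wrong if taken literally and ambiguous otherwise. Its demonstrated cost is modest: fitted values can fall outside 0 to 1 and the variance is not constant, while the single-visit test behaves close to nominal. Harm in the repeated-measures model has not been shown. For the four lesion outcomes the fault is an undefined summary, not a proven loss.

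The primary analysis, a stratified Cochran-Mantel-Haenszel test, is untouched. These are corrections that should be made to secondary analyses; they do not threaten the main conclusion.

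**What to change.** - **Quality of life.** Make the between-arm comparison a mixed model on the CADI and EQ-5D scores, with visit, visit-by-arm, baseline score and contraception stratum. Keep percent improved as a descriptive row for each instrument, with a stated threshold.
- **Binary endpoints.** Replace general linear by a generalised (logistic) mixed model or GEE for the AFAST 0-or-1 and remission endpoints.
- **Lesions.** Restrict the sentence on percentages to the five outcomes that count patients. State that the three face-lesion numbers are compared as counts and ECLA F2 as a score.

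The data and visits stay the same. The cost is a few sentences in Outcomes {12} and section {20a}, and slightly more programming.

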### Participant timeline {13}

The maximum duration of treatment per patient is 12 months, and the recruitment period is 41 months.

### Sample size {14}

For sample size estimation purposes, the targeted difference in the percentage of success is 70% in the experimental arm compared with 50% success in the control arm, indicating a relative increase in success equal to 40%. Assuming a type I error rate of 5% and at least 80% statistical power, the sample size required is at least 91 subjects per group. To take into account the possibility of patients being lost to follow up, 10% (9 subjects) will be added to each group. Finally, approximately 200 subjects will be randomized to the two arms in a 1:1 ratio.

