### Methods in analysis to handle protocol non-adherence and any statistical methods to handle missing data {20c}

All participants will receive the assigned study treatment until unacceptable toxicity, death, loss to follow up, withdrawal of consent or termination of the study by the Sponsor, in accordance with local standards of care. Unacceptable toxicity and death will be considered as failure for the primary criteria analysis. Loss to follow up, missing data for the primary criteria and early termination of the study by the Sponsor will be also considered as failures by the ITTm and not replaced.

Patients who did not fulfil the inclusion criteria after randomization and those who never began their treatment will be replaced. For the clinical secondary criteria analysis, patients with missing data will be withdrawn. Missing data in cost-effectiveness analysis will be handled according to a multiple imputation method in the ITTm sample. If a patient is released from the study (e.g. in the event of adverse reactions (ARs) preventing the continuation of the study), her data will not be collected, except for safety data (follow up of ARs or onset of ARs associated with the experimental treatment, based on pharmacokinetic data).

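### The 10% allowance for loss to follow-up does not protect the stated 80% power, because the primary analysis keeps lost patients as failures; the protocol should restate the power or say what 70% and 50% mean

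*Protocol article*

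**What the plan says.** Under Sample size {14}, the protocol article says that "the targeted difference in the percentage of success is 70% in the experimental arm compared with 50% success in the control arm". It continues: "Assuming a type I error rate of 5% and at least 80% statistical power, the sample size required is at least 91 subjects per group". The next step is the allowance: "To take into account the possibility of patients being lost to follow up, 10% (9 subjects) will be added to each group". This gives 100 per arm, and "approximately 200 subjects will be randomized to the two arms in a 1:1 ratio".

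The test is two-sided according to Statistical methods {20a}: "Significance will be set at 5% in a bilateral situation". The same section sets the primary analysis as modified intention to treat. Everyone randomized is included except women found not to meet the inclusion criteria and women who never started treatment.

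The section on non-adherence and missing data {20c} lists "Loss to follow up, missing data for the primary criteria and early termination of the study" by the sponsor among the events that count as failure for the primary criterion, and says these patients are not replaced. The two groups that do leave the analysis set, the ineligible and the never treated, are replaced.

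**The concern.** Inflating a sample size for loss makes up for patients who drop out of the denominator: recruit 100, lose about 10%, analyse about 90. In this trial the denominator does not shrink. A lost woman stays in it as a non-success. The cost of loss is therefore a smaller treatment difference, not a smaller sample, and the calculation makes no allowance for that. Nor are the 9 extra needed for women excluded from the modified intention-to-treat set, since those women are replaced.

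The trial has one primary superiority test and no interim analysis. The protocol tells its reader that a 20-point advantage would be detected with at least 80% probability. If that probability is lower under the protocol's own loss figure and its own failure rule, the stated type II error is wrong.

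**Working it through.** **Inputs.** From Sample size {14}: success 70% and 50%, type I error 5%, power at least 80%, 91 per arm before and 100 after the allowance, 10% loss. From {20a}: two-sided testing. From {20c}: losses scored as failures. The planned Cochran–Mantel–Haenszel test is approximated by an unstratified two-proportion test. The unstratified formula in step 1 also returns the protocol's 91, so the comparison is like for like.

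**1. Reproduce the 91.** Unpooled normal approximation:

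n = (1.960 + 0.842)² × (0.70×0.30 + 0.50×0.50) / 0.20² = 7.849 × 0.46 / 0.04 = 90.3, rounded up to 91.

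The figure is correct. The pooled-variance version gives 93.

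**2. The case the allowance fits.** If 10 of 100 per arm were lost and excluded, 90 per arm at 70% against 50% would give 79.9% (unpooled). That is the stated target.

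**3. The case the analysis rule creates.** Suppose a proportion d of each arm is lost and scored as failure, and 70% and 50% apply to the rest. The rates become 0.70(1 − d) and 0.50(1 − d), with 100 per arm still analysed. For d = 10%:

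- rates 0.63 and 0.45, difference 0.18
- standard error = √[(0.63×0.37 + 0.45×0.55)/100] = √[(0.2331 + 0.2475)/100] = 0.0693
- 0.18 / 0.0693 = 2.596
- power = Φ(2.596 − 1.960) = 73.8%

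The pooled formula gives 72.7%. A simulation of the uncorrected chi-square test (400,000 replicates) gives 74.2%.

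**4. Range of loss, equal in both arms, 100 per arm.**

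| Loss scored as failure | Rates | Power, unpooled | Power, pooled |
|---|---|---|---|
| 0% | 70% v 50% | 83.9% | 82.8% |
| 3% | 67.9% v 48.5% | 81.0% | 79.9% |
| 4% | 67.2% v 48.0% | 80.0% | 78.9% |
| 5% | 66.5% v 47.5% | 79.0% | 77.9% |
| 10% | 63.0% v 45.0% | 73.8% | 72.7% |
| 15% | 59.5% v 42.5% | 68.4% | 67.4% |

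So 80% is kept up to about 4% loss (unpooled) or 3% (pooled), well short of the 10% the protocol plans for.

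**5. Size that would hold 80% at 10% loss.** 7.849 × (0.2331 + 0.2475) / 0.18² = 116.4, so 117 per arm (unpooled), or 120 pooled. This only shows the gap; the fix does not ask for it.

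**6. Unequal loss (assumed; the protocol gives no loss by arm).** With 10% lost on control and 5% on spironolactone, the rates are 66.5% v 45.0% and pooled power is 87.0%. With 5% on control and 10% on spironolactone, they are 63.0% v 47.5% and pooled power is 59.8%.

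**The case against.** The strongest reply is that 70% and 50% may already be modified intention-to-treat rates, with losses counted as failures. The sample size section does not define them, and {20a} speaks of maintaining the initial power of that very analysis. On this reading 100 per arm gives about 83–84% and power is not short. This stands as a possibility, but it does not rescue the text: if losses were already inside the rates, there would be no reason to add 9 patients for loss. The allowance points to rates among observed patients, without settling it.

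Second, 10% lost need not mean 10% extra failures. The endpoint is the best response at month 4 or month 6, so a woman lost after a successful month 4 visit may already have a usable success. {20c} does not say when a loss must occur to count as failure. If half of a 10% loss came after such a visit (an assumption), about 5% would be forced failures and power would be 78–79%. This also stands, and it makes the shortfall small in that case.

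Third, equal loss is an assumption, and unequal loss moves power in either direction, as step 6 shows.

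A reader might therefore infer that the design simply delivers 74%. The documents do not support that as a flat statement; it is one scenario under three conditions. A reader might also fault the rule that scores early termination by the sponsor as failure. That is a separate, contingent matter, it contributes nothing to the power figures here, and no change to it is proposed.

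**Conclusion.** The point holds in conditional form. The 91 is right. The reason given for going from 91 to 100 is inconsistent with how lost patients are analysed, whichever meaning 70% and 50% have.

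If they are rates among women with an observed outcome, loss is 10% in each arm, and every loss is a non-success, planned power is about 73–74%: some 6 to 7 points below the claim, or a type II error of about 26–27% instead of 20%. A smaller effective loss shrinks the gap, and a loss of up to 3–4% closes it. If the rates already include losses as failures, power is about 83–84% and only the stated reason for the extra 9 is wrong.

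The primary test, its type I error, the analysis set and the definition of success are not affected.

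**What to change.** Revise the sample size paragraph in one of two ways.

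- **If 70% and 50% are rates among women with an observed outcome:** say so, and restate the power under the failure rule. For example: with 100 per arm and 10% per arm scored as failures (63% against 45%), power is about 74%; it is about 78–79% at 5% and 67–68% at 15%, assuming equal loss in both arms.
- **If 70% and 50% already count losses as failures:** say so, remove loss to follow-up as the reason for the extra 9 per arm, and quote about 83–84% power at 100 per arm.

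The cost is wording in one paragraph. Under the first option the stated power becomes less favourable. Neither option needs extra patients or a change to the primary analysis.
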